### Questionnaire Validity and Reliability

Before the deployment of the questionnaire for field use, face validity and qualitative content validity will be determined by a panel of experts in oral and maxillofacial surgery, dental public health, biostatistics, and laypersons. The internal consistency of the scales used to measure e-cigarette smoking exposure will be determined using Cronbach α, with a minimum α value of .70 indicating good and acceptable reliability.

### Data Analysis

Descriptive statistics will be used for all binary, categorical, and continuous variables and expressed as tables, texts, and figures. Bivariate analysis will then be performed for relevant variables. The Shapiro-Wilks test will be performed for continuous variables to determine whether they follow the Gaussian distribution. Afterward, the independent 1-tailed *t* test and 1-way ANOVA will be used; otherwise, the Mann-Whitney *U* test and Kruskal-Wallis test will be performed. For cross-tabulation of 2 categorical variables, the chi-square test will be used. Variables that do not fulfill the assumption of this test will be analyzed using Fisher exact test. Comparisons with *P*=20 will be used to implement multivariable analysis using multiple logistic regression. Odds ratios and 95% CIs will be determined for e-cigarette smoking and other individual factors. For all analyses, *P*<.05 will be used to denote statistical significance. Statistical analyses will be performed using the SPSS (version 27; IBM Corp).

The control and e-cigarette groups will be subjected to a *t* test (assuming the data meet the normality criteria and do not meet the criteria for the rank sum test) to verify whether e-cigarettes cause harm.

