**Objective:**

This aims to determine whether e-cigarettes cause damage to the oral mucosa. This study also aims to evaluate the association between e-cigarette smoking and oral mucous membrane lesions in young adults. The objectives are to (1) compare the oral mucosal conditions in participants with and without e-cigarette smoking habits, (2) assess the effect of the amount of e-cigarette smoking on oral mucosal conditions, and (3) assess the effect of the duration of e-cigarette smoking on oral mucosal conditions.

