### Hypothesis

This study hypothesizes that e-cigarettes, in the speculated absence of tobacco, may still induce carcinogenesis. Alternatively, it is suggested that this habit may trigger an imbalance in the oral microbiome that predisposes the mucosal epithelium to oral cavity cancer with other etiological factors. This presupposed risk is likely proportional to the frequency and duration of e-cigarette smoking. The oral mucosal health of participants will be determined by determining the presence of white spots in the mouth (the main feature of the oral mucosa that is damaged by smoking behavior).

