### Data Collection: Questionnaire

Interviewer-administered questionnaires will be used to collect data on demographic, lifestyle, and socioeconomic variables for the cases and controls. The questionnaire tool will comprise 2 parts: exposure information (part A) and sociodemographic information (part B). A life grid sheet will be used during interviews to efficiently collect retrospective information on lifestyle habits and other risk factors. To reduce observer bias, interviewers will not initially be informed about the aim of the research. Once cases are identified and interviewed, matching controls will be recruited and interviewed. Answers provided by participants will be converted to objective scores after data collection by the investigator (SC). The details on the parts of the questionnaire are as follows.

Exposure information (part A) will include (1) oral mucosal health status (whether white spots are present), (2) smoking habits, (3) type of products used, (4) e-cigarette smoking status (yes or no and current or previous), (5) age of onset, (6) duration of smoking, (7) pattern of smoking duration (continuous or intermittent), (8) frequency of smoking (daily, weekly, and occasionally), (9) number of cartridges (frequency), and (10) Tobacco consumption. Sociodemographic information (part B) will include (1) age, (2) sex, (3) occupation type, (4) education level, (5) income, and (6) ethnicity.

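### The hypothesis is that risk rises with frequency of use, but the rule for categorical variables sends the ordered frequency item to a chi-square or Fisher test that ignores the order

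*Protocol article*

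**What the plan says.** The Hypothesis section of the protocol article states a direction and a shape: "This presupposed risk is likely proportional to the frequency and duration of e-cigarette smoking". The second objective in the abstract is to "assess the effect of the amount of e-cigarette smoking on oral mucosal conditions".

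Under Data Collection: Questionnaire, two items bear on amount. One is "frequency of smoking (daily, weekly, and occasionally"), which has three ordered levels. The other is "number of cartridges (frequency"), which is a count. The outcome is binary: "oral mucosal health status (whether white spots are present").

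Data Analysis assigns tests by type of variable. For two categorical variables: "For cross-tabulation of 2 categorical variables, the chi-square test will be used". The fallback is: "Variables that do not fulfill the assumption of this test will be analyzed using Fisher exact test". Continuous variables get a t test or ANOVA if normal; "otherwise, the Mann-Whitney *U* test and Kruskal-Wallis test will be performed". The bivariate results then decide which variables enter a multiple logistic regression that reports odds ratios with 95% CIs.

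**The concern.** Frequency by white spots is a cross-tabulation of two categorical variables, so the stated rule sends it to Pearson's chi-square or Fisher's exact test. With three levels, both ask whether the levels differ in any way (2 df for the chi-square). Neither uses the fact that daily is more than weekly and weekly more than occasional. That ordering is the substance of the hypothesis.

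Two things follow. If risk does rise with frequency, the test spends a degree of freedom on patterns nobody has proposed and has less power than a test aimed at a trend. And a significant result would not show that risk rises with use, because a non-monotone pattern can produce it just as readily. Only about 152 × 0.11 = 16.7 lesions are expected among users, so there is little information to give away.

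**Working it through.** **Plan's own figure.** The article gives no power for the frequency analysis. Its only design figure is 152 per group for 11% against 2.5% at 80% power and P=.04 (Sampling Methods). The usual two-proportion formula (pooled variance, two-sided .04, no continuity correction) gives 145 per group, and 152 per group has 81.9% power. The appendix with the calculation is not shown, so the gap may reflect an allowance made there. That figure concerns users against controls and does not bear on this point.

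**Inputs from the article.** 152 users; 11% lesion risk among users; three frequency levels; binary outcome; significance at P<.05.

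**Assumptions.** Two-sided testing; analysis among users only; the split across levels (written occasional/weekly/daily); and the gradient. The article gives none of these for this analysis, so a range is shown.

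**Risks.** For a daily-to-occasional ratio R with linear risk, weights are w = 1, (1+R)/2, R, and p_i = 0.11 × 152 × w_i / Σ n_j w_j. For 51/51/50 and R = 3: Σ n w = 51 + 102 + 150 = 303, and 16.72/303 = 0.0552, giving risks of 5.5%, 11.0% and 16.6%.

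**Tests.** With x_i lesions among n_i users, pooled proportion p̂, scores s = 1, 2, 3 and s̄ = Σ n_i s_i / 152:
- Pearson: X² = Σ (x_i − n_i p̂)² / [n_i p̂(1 − p̂)], critical value 5.99 (2 df).
- Cochran-Armitage: Z² = [Σ (s_i − s̄) x_i]² / [p̂(1 − p̂) Σ n_i (s_i − s̄)²], critical value 3.84 (1 df).

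**Hand check, 51/51/50 at R = 3.** Noncentrality is about (51 × 0.0548² + 50 × 0.0555²)/(0.11 × 0.89) ≈ 3.1. At noncentrality 3 a 2-df test has 32.2% power and a 1-df test 41.0%.

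**Simulation (40,000 runs per scenario), power of Pearson → trend, %:**

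| Split | R = 2 | R = 3 | R = 6 | R = 10 |
|---|---|---|---|---|
| 51/51/50 | 15.8 → 21.6 | 32.5 → 42.7 | 63.9 → 74.8 | 79.3 → 87.2 |
| 38/38/76 | 11.3 → 18.4 | 23.0 → 35.9 | 45.2 → 63.0 | 59.1 → 76.5 |
| 76/38/38 | 21.4 → 26.1 | 45.4 → 53.3 | 82.8 → 87.5 | 94.6 → 96.3 |
| 30/46/76 | 9.2 → 14.9 | 17.2 → 28.8 | 33.3 → 51.8 | 43.5 → 64.1 |
| 90/40/22 | 22.4 → 25.6 | 46.7 → 53.1 | 86.1 → 89.5 | 96.7 → 97.8 |

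The loss runs from about 1 point (90/40/22, R = 10) to about 21 points (30/46/76, R = 10). With no effect (equal thirds), rejection is 4.7% for Pearson and 5.0% for trend, so the gain is not bought with false positives. Where expected counts are small (30 × 0.11 = 3.3 in the smallest level of 30/46/76), the plan may switch to Fisher's test; its three-level form loses about 1 to 14 points over the scenarios run.

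**Which pattern is detected.** For equal thirds, Pearson rejects 32% of the time under a rising 1:2:3 gradient and 33% when weekly users are worst (1:3:2). The trend test rejects 43% and 11%.

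**Patterns that are not linear.** With risks of 5%, 5% and 23% in equal thirds: 82.4% against 82.9%. With 5%, 14% and 14%: 30.0% against 28.8%. With 1:1:3, over five splits, the trend test ranges from 6 points worse to 9 points better.

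**Screening step.** The entry threshold is printed as P=20. If .20 is meant (an assumption), frequency passes 62% of the time with Pearson and 71% with trend (equal thirds, 1:2:3), or 55% and 65% (38/38/76).

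**The case against.** The best defence is that the chi-square sentence is a general rule that names neither frequency nor the second objective. The questionnaire section says answers will be turned into scores, and the reliability section speaks of exposure scales. A scored frequency could go to the Mann-Whitney test, which uses order; for a binary outcome it is close to a trend test (43.0% power for both with equal thirds at 1:2:3, and within about 3 points in every graded scenario). This does not remove the problem. No scoring of frequency is described, and as collected the item is categorical.

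A second defence is the logistic regression, where an ordered term is not excluded. That stands as a possibility, and unstated coding is not itself a fault in an article. But bivariate results decide entry, so the unordered test can drop frequency before any ordered term is fitted.

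A reader might infer that the whole second objective loses power, or that the loss is a fixed number of points. The documents support neither. Amount is also measured by cartridges, which as a count would get order-sensitive tests. The size of the loss depends on a split and a gradient that the article does not give.

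It also stands that this is one item, in one step, for an objective the sample size was not set to address.

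**Conclusion.** The point holds for the bivariate analysis of the frequency item. The hypothesis is ordered, the item is ordered, and the test that the stated rule assigns ignores order, so a significant result would not by itself support a rising risk.

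The cost in power is conditional: about 1 to 21 points for the chi-square test with 152 users, 11% overall risk, two-sided .05 and linear risk with a ratio of 2 to 10. It is little, nil or reversed if only daily users are at risk, but that is not the pattern hypothesised.

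The change is worth making because it is cheap. The comparison of users with controls is unaffected. The fix does not rescue the dose question: at 1:1.5:2 the trend test itself has only about 14% to 26% power over the splits examined (which also included 61/30/61 and 30/92/30).

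**What to change.** In Data Analysis, add that white spots by frequency of use will be tested among users with a 1-df trend test: Cochran-Armitage, or linear-by-linear association in SPSS, in its exact form when expected counts are small. Fix the scores in advance as occasional = 1, weekly = 2, daily = 3. Use this test for the frequency item at the screening step. In the logistic regression, enter frequency as an ordered score and report the odds ratio per step with its 95% CI. Keep the 2-df chi-square as a descriptive check for departure from trend.

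The cost is a sentence or two of wording. SPSS prints the linear-by-linear statistic alongside the chi-square, no new data or participants are needed, and the article reports that no data have been collected. The one downside is lower power if the true pattern is not monotone; the retained 2-df test would help to show such a pattern.

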### Sampling Methods

Convenience and nonprobability sampling methods will be used for the recruitment of cases and controls. The detailed sample size determination is shown in Multimedia Appendix 1 [16]. Briefly, the predefined power is 80% (*P*=.04), and the predefined proportions of the case and controlled groups are 11% and 2.5%, respectively. In all, 304 youths aged 15 to 24 years (n=152, 50% who smoke only e-cigarettes and n=152, 50% who do not smoke e-cigarettes or cigarettes) will be recruited.

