## Discussion

In examining the potential negative impact of e-cigarettes on the oral mucosa, this study deliberately focused its investigation on this specific aspect, excluding other potential confounding factors that might influence the results. Notably, variables such as alcohol consumption, daily routines, and gender differences were not considered in the experimental design. While these factors were omitted from this study, they were duly documented in the questionnaire phase, laying the groundwork for future investigations to delve into these variables. This strategic choice aimed to isolate the primary relationship between e-cigarette use and oral mucosal health, with the intention to refine and expand the scope in subsequent research endeavors.

The findings of this study align with existing literature on e-cigarettes, which suggests a correlation between the chemicals present in e-cigarettes and cytotoxicity, leading to damage to the oral mucosa. This corroborates with prior research, providing further evidence of the potential harm associated with e-cigarette use [10,16,17]. The recognition of this association holds significant implications for public health, emphasizing the need for awareness campaigns and regulatory measures to mitigate the adverse effects on oral health. Moreover, the study acknowledges the diverse landscape of e-cigarettes in the United States, encompassing various brands and flavors, each containing distinct chemical compositions. Given this complexity, it is acknowledged that the study does not comprehensively analyze all individual chemicals present in different e-cigarettes. This limitation prompts a call for future experiments to undertake a more nuanced examination of the diverse chemical profiles within e-cigarettes to better understand their distinct impacts on oral mucosal tissues.

Despite the valuable insights provided by this study, certain limitations should be acknowledged. The decision to exclude factors such as alcohol consumption and daily routines may have implications for the generalizability of the findings. In addition, the complexity of e-cigarette compositions poses a challenge, as the study did not extensively investigate the myriad chemicals present in different e-cigarette products. Future research endeavors should consider a more comprehensive approach, encompassing a broader range of variables and a detailed analysis of the chemical constituents of various e-cigarettes.

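### The covariate entry rule is impossible as printed (P=20). Read as P<.20 it would often drop real confounders with about 20 expected lesions, and the Discussion conflicts with the adjusted model.

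*Protocol article*

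**What the plan says.** Data Analysis describes bivariate tests followed by a multivariable step: "Comparisons with *P*=20 will be used to implement multivariable analysis using multiple logistic regression". It then promises that "Odds ratios and 95% CIs will be determined for e-cigarette smoking and other individual factors". The same section also names an unadjusted t test between the two groups as the check on whether e-cigarettes cause harm.

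The Questionnaire section lists these sociodemographic items: "1) age, (2) sex, (3) occupation type, (4) education level, (5) income, and (6) ethnicity". Alcohol is not among the itemised questions in either part.

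The Discussion describes the study as "excluding other potential confounding factors that might influence the results". It names alcohol, daily routines and gender as left out, says they were nonetheless recorded in the questionnaire, and explains: "This strategic choice aimed to isolate the primary relationship between e-cigarette use and oral mucosal health".

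Selection of Controls requires no history of alcohol drinking. The criteria for the e-cigarette group contain no alcohol rule.

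**The concern.** The entry rule is the only statement of what the adjusted model contains, and it cannot be executed. Other P values in the article keep their decimal point (P=.04 for the sample size; "For all analyses, *P*<.05 will be used to denote statistical significance"), so this is probably a misprint. Even P=.20 would still lack an inequality.

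Correcting the misprint does not remove the problem. A covariate confounds because it is related to both exposure and lesion. Whether it reaches a P threshold against the lesion in one small sample is mostly a question of power. With few lesions, real confounders will fail by chance and the adjustment set will vary from sample to sample. The groups come from e-cigarette stores and passers-by, so differences in age, sex and habits are to be expected.

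The Discussion adds a second difficulty. It presents leaving confounders out as a way to isolate the effect, whereas in an observational comparison that leaves their influence inside the estimate. It also disagrees with a Methods section that promises adjusted odds ratios.

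**Working it through.** **Inputs from the protocol (Sampling Methods).** 152 per group, with "the predefined proportions of the case and controlled groups are 11% and 2.5%, respectively". Power is 80% at P=.04, sidedness not stated.

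**The plan's own figure.** The pooled normal formula is n = [z(1−α/2)·√(2p̄q̄) + z(0.8)·√(p₁q₁+p₂q₂)]² / (p₁−p₂)². With p₁=0.11, p₂=0.025, p̄=0.0675 and two-sided α=.04:

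(2.054×0.3548 + 0.8416×0.3497)² / 0.085² = 1.046/0.007225 ≈ 145 per group.

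A two-sided Fisher exact test reaches 80% power at about 148 per group (α=.05) or 156 (α=.04). At 152 its power is 81.5% or 78.9%. The planned size is therefore consistent with its inputs and is not at fault here.

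**Expected lesions.** 152×0.11 + 152×0.025 = 16.7 + 3.8 = 20.5.

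**Chance that P<.20 drops a factor.** The documents give no covariate effects or prevalences, so these are assumed. A binary covariate has a given odds ratio (OR) for lesion and a given prevalence in the e-cigarette and control groups. In each group the baseline b is solved from prevalence×expit(b+ln OR) + (1−prevalence)×expit(b) = 0.11 or 0.025, which keeps the planned lesion rates. The covariate is tested against lesion status by chi-square (4,000 simulated studies per setting, Monte Carlo error about 1 percentage point). Data Analysis does not say what the bivariate comparisons are against; lesion status is the usual form and is assumed.

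| Prevalence, e-cigarette/control | OR 1.5 | OR 2 | OR 3 |
|---|---|---|---|
| 60%/35% (positive confounder) | about 38% | about 21% | about 6% |
| 50%/50% (balanced risk factor) | about 66% | about 44% | about 17% |
| 35%/60% (negative confounder) | about 79% | about 71% | about 43% |

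The bottom row is worst because 16.7 of the 20.5 expected lesions fall in the e-cigarette group. A risk factor commoner among controls has its crude association masked. The middle row shows the screen's low power; a perfectly balanced factor does little harm if dropped.

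**What a dropped confounder does.** Treating the OR as a risk ratio because lesions are uncommon, the distortion is [1+p₁(OR−1)]/[1+p₂(OR−1)], with p₁ and p₂ now the covariate prevalences. For OR 2 at 60%/35% this is 1.60/1.35 = 1.19; at 35%/60% it is 1.35/1.60 = 0.84. For OR 3 it is 2.2/1.7 = 1.29 and 1.7/2.2 = 0.77.

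**The opposite risk.** If all six sociodemographic variables pass and use one coefficient each, the model with e-cigarette status has 20.5/7 ≈ 2.9 lesions per coefficient, and fewer when categories are expanded.

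**Adding alcohol under the present criteria.** Every control would be a non-drinker. In a main-effects model the e-cigarette odds ratio would then rest on non-drinking e-cigarette users against controls. If 50% to 80% of users drink (assumed) and non-drinking users keep an 11% lesion rate, the users' informative lesions fall from 16.7 to 152×0.5×0.11 = 8.4 or 152×0.2×0.11 = 3.3. The standard error of the log odds ratio rises from √(1/16.7+1/135.3+1/3.8+1/148.2) = 0.58 to 0.64 or 0.78, about 10% to 34%.

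**The case against.** P=20 is an obvious slip, and on its own it needs only a correction. That is fair; the weight lies in the screen behind it.

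The size of the loss rests on assumed covariates, and strong positive confounders are seldom lost (about 6% at OR 3). This also stands. The claim is that the screen would often drop moderate confounders, not that it always would.

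A reader might infer that e-cigarette status itself could be screened out of the model. The documents do not support this. The next sentence promises an odds ratio for e-cigarette smoking, and at 11% against 2.5% it would pass P<.20 in about 97% of samples.

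A reader might also infer that confounding is wholly ignored. Tobacco smokers are excluded from both groups, and the Recruitment Strategy and Questionnaire sections refer to matching controls, though without naming matching factors. The Discussion partly frames the omission as a matter of design and lists it as a limitation. But it also speaks of the factors as left out of the study, which reaches beyond design, and it offers this as a means of isolating the effect. The two sections still have to be reconciled.

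Finally, the life grid in the Questionnaire section might capture alcohol under lifestyle habits. Possibly so, but the itemised list does not name it, so the Discussion's statement that it was documented cannot be confirmed.

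**Conclusion.** The point holds. The entry rule is wrong as printed. In its likely form it is unsuited to about 20.5 expected lesions: a factor with OR 1.5 to 2 is dropped in about 21% to 79% of samples and one with OR 3 in about 6% to 43%, with the highest loss for negative confounders. These ranges assume the planned lesion rates, binary covariates at the prevalences shown, and screening against lesion status. In the imbalanced settings worked above, one missed confounder would move the estimate by roughly 16% to 29% in either direction.

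The Discussion contradicts the adjusted model in Data Analysis and misdescribes what omitting confounders achieves. A tempting further step is to say that alcohol merely needs adding to the model. It does not follow, because the alcohol criterion applies to controls only.

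**What to change.** - Delete the P-value screen from Data Analysis. Prespecify one logistic model containing e-cigarette status, age and sex, plus any factors used to match controls, all kept regardless of P value. Fit it by Firth penalised likelihood. Allow further covariates only in a labelled sensitivity model.
- Reconcile the alcohol criterion between the two groups and name alcohol as a questionnaire item before it enters any model. Otherwise limit the main comparison to non-drinkers, which also needs alcohol recorded in the e-cigarette group.
- Rewrite the Discussion to state which confounders are adjusted for and which remain uncontrolled, and remove the statement that leaving them out isolates the effect.

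**Cost.** No data have been collected, so this is mainly wording plus one questionnaire item; age and sex are already collected. The interval will be somewhat wider than the unadjusted one. Three to four coefficients leave 20.5/3 ≈ 6.8 to 20.5/4 ≈ 5.1 lesions each, which is thin and is the reason for penalisation. Firth fitting may need an add-on to the named software. Limiting the comparison to non-drinkers would mean recruiting more widely or accepting less precision.

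### Amount and duration of e-cigarette use are not exempted from the bivariate P screen for the logistic model, so Objectives 2 and 3 have no guaranteed adjusted estimate

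*Protocol article*

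**What the plan says.** The Objective section of the abstract lists three aims. The second is to "assess the effect of the amount of e-cigarette smoking on oral mucosal conditions" and the third is to "assess the effect of the duration of e-cigarette smoking on oral mucosal conditions".

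The Data Analysis section sets out a sequence. First, "Bivariate analysis will then be performed for relevant variables", using t tests, ANOVA, rank tests, chi-square or Fisher tests. Then the comparisons that meet a criterion printed as P=20 "will be used to implement multivariable analysis using multiple logistic regression". The printed threshold is not a possible P value; the usual screening level of this form would be P<.20. The sentence does not separate study exposures from covariates and exempts nothing.

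The next sentence reads: "Odds ratios and 95% CIs will be determined for e-cigarette smoking and other individual factors". It attaches no screening condition and does not say whether the odds ratios are crude or adjusted. Amount and duration are not named in it or anywhere else in the section.

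**The concern.** A P-value screen decides which covariates to carry forward. Applied to an exposure that is itself a study question, it makes the reporting of the answer depend on the answer. Estimates that survive are, on average, too far from no effect, and those that fail have no adjusted odds ratio or interval. A reader then cannot see which effects remain compatible with the data.

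This matters here because the Hypothesis section expects risk to rise with frequency and duration of use, and the Research Significance section says the results may either implicate e-cigarettes or rule them out. A dose-response claim should not be selected for being large, and a negative claim needs an interval. The issue is separate from which confounders the screen keeps.

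**Working it through.** **Inputs from the protocol article (Sampling Methods).** There are 152 users and 152 controls, power is 80% at P=.04, and "the predefined proportions of the case and controlled groups are 11% and 2.5%, respectively".

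**Assumptions not in the document.** The screen is two-sided P<.20. Lesions occur in 11% of users. Amount and duration are analysed among users, per SD of dose, with one predictor.

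**1. The plan's own figure.** Two-proportion power with pooled variance under the null:
- Pooled proportion (0.11+0.025)/2 = 0.0675; null term √(2×0.0675×0.9325) = 0.3548; alternative term √(0.11×0.89+0.025×0.975) = 0.3497; difference × √n = 0.085×√152 = 1.048.
- At two-sided .04: (1.048 − 2.054×0.3548)/0.3497 = 0.913, so power is 81.9%, consistent with the stated 80%.

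**2. Objective 1 under the screen.** The same formula at two-sided .20 gives (1.048 − 1.282×0.3548)/0.3497 = 1.697, so user status passes 95.5% of the time at the planned difference (Fisher exact 94.8%; a separate simulation 97%). Little is lost, even if user status were screened.

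**3. Objectives 2 and 3, by hand.**
- Expected lesions among users: 152×0.11 = 16.7, about 17.
- Approximate standard error of the log odds ratio per SD: 1/√(152×0.11×0.89) = 1/√14.88 = 0.259.
- To pass P<.20, the estimate must exceed 1.282×0.259 = 0.332 in absolute value, i.e. an odds ratio above about 1.39 or below about 0.72. Any smaller effect that is kept must therefore be overstated or have the wrong sign.
- True odds ratio 1.2 (log 0.182): upper tail beyond (0.332−0.182)/0.259 = 0.58 is 0.28; lower tail beyond (0.332+0.182)/0.259 = 1.98 is 0.02. It passes about 30% of the time.
- True odds ratio 1.5 (log 0.405): (0.332−0.405)/0.259 = −0.28. It passes about 61% of the time.
- No effect: passes about 20% by construction, so it is left out about 80% of the time.

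**4. Simulation (normal and exponential dose, 152 users, 11% lesions).** Ranges run across the dose shapes and runs.

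| True odds ratio per SD | Kept by screen | Odds ratio when kept |
|---|---|---|
| 1.0 | 18-20% | 95% CI coverage falls to 76-80% |
| 1.2 | 30-33% | median 1.48-1.60 |
| 1.5 | 60-70% | median 1.65-1.76 |
| 2.0 | 89% (normal dose) | average 2.17 |

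With a normal dose and the exposure always reported, the average estimates are 0.99, 1.20, 1.51 and 2.05 for the four rows, with 95-96% coverage.

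**5. Sensitivity to the threshold.** Using the same standard error:
- P<.10: the smallest upward estimate kept is exp(1.645×0.259) = 1.53; a null is left out 90% of the time; a true 1.2 is kept about 18%.
- P<.25: the smallest is exp(1.150×0.259) = 1.35; a null is left out 75% of the time; a true 1.2 is kept about 36%.

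**The case against.** The strongest reply is that the text does not say amount and duration would be dropped. The odds-ratio sentence carries no condition, crude odds ratios are not ruled out, and its reference to other individual factors can be read to include both exposures. Forcing exposures into a model is also a detail that an analysis plan often supplies. Part of this stands: the filtering follows from applying the stated rule literally, and only the adjusted estimate is at risk. But the article does fix an entry rule, without exception, and an analyst who followed it would leave out a weak duration effect.

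Three stronger readings are tempting and not supported:
- **That a null result gets no interval, so Objectives 2 and 3 go unanswered.** On the P<.20 reading, a non-significant result with P between .05 and .20 is still kept, about 20% of true nulls pass, and descriptive statistics are promised for all variables.
- **That Objective 1 is distorted too.** An odds ratio for e-cigarette smoking is promised without condition, and at 11% versus 2.5% user status would pass 95-97% of the time.
- **That kept estimates are always exaggerated.** The inflation is about 10-17% at a true 1.5 (1.65/1.5 = 1.10; 1.76/1.5 = 1.17) and nearly gone at 2.0.

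It is also fair to say that the percentages rest on assumptions. The assumed mean duration does not matter, because dose is standardised. The shape does, which is why ranges are given.

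**Conclusion.** The point holds in a limited form. The Data Analysis section states an entry screen with an unusable printed threshold and does not exempt the exposures of Objectives 2 and 3, so these have no guaranteed adjusted estimate. Taken literally, the rule would often leave null-to-moderate dose effects out of the adjusted model and overstate those it kept: by roughly a quarter to a third at a true 1.2 (1.48/1.2 = 1.23; 1.60/1.2 = 1.33), and hardly at all at 2.0. Objective 1 is little affected.

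The direction follows from the screen itself. The sizes depend on two-sided P<.20, 11% lesions among users, the dose distribution and a single-predictor model; an adjusted model with few events could behave differently.

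**What to change.** Add one sentence to Data Analysis: user status (all 304 participants), and amount and duration of e-cigarette smoking (among users), are entered in the logistic models and reported with odds ratios and 95% CIs whatever their bivariate P value; any screen that is kept applies to covariates only. Correct the printed P=20 to an actual threshold at the same time.

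No data have been collected, so the change needs no new measurements and no change in sample size. Its downside is that some non-significant and imprecise estimates must be shown, which with about 17 lesions among users is the honest result.
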